### Study design

This study will be a randomized, placebo-controlled, crossover design, investigator-initiated clinical trial. The trial will be conducted at Pusan National University Korean Medicine Hospital. Thirty healthy male adults will be recruited via hospital bulletin boards and local advertisements. Subjects who voluntarily wish to participate in this study and provide written informed consent will undergo a screening assessment to determine their eligibility. Subjects will be hospitalized for 4 days. On the first day, the subjects will perform eccentric exercise for 1 h to induce DOMS. After exercise, the subjects will be administered either JGT or placebo for 3 days. After a more than 1 week wash-out period, the subjects will repeat the same process with the other drug. The duration of the wash-out period was calculated based on the major component of JGT with the longest half-life. As glycycoumarin has the longest half-life (*T*_1/2_) of 14.9 h [20], we decided that the wash-out period should be 6.21 days or more, which is 10 times the half-life of glycoumarin needed to minimize the carry-over effect of JGT. The overall study flow is shown in Fig. 1. A detailed schedule is given in Fig. 2 and Table 1.

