### Randomization and allocation concealment

Subjects will be randomly allocated to either the JGT or the placebo group with equal probability. An independent statistician will use SAS version 9.4 software (SAS Institute, Cary, NC, USA) to generate a random allocation list and will send the list to the pharmaceutical company for packing. The random allocation list will assign 30 subjects to group A or B. According to the crossover design, both groups will take JGT and the placebo drug. Subjects in group A will take JGT and those in group B will take the placebo drug during their first hospitalization.

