### Exercise protocol for inducing muscle soreness

A standardized treadmill exercise protocol will be performed on the first day of hospitalization to induce DOMS. Previous studies have shown that a downhill running protocol induces stress in the gastrocnemius muscles, as it is an unfamiliar eccentric exercise [29–31]. The subjects will step backwards on a moving treadmill inclined at 13°. Starting with the right leg, the subjects will continue the exercise for 1 h at a speed of 2.2 km/h. The subjects will carry a 5–10 kg weight belt to ensure adequate stimulation to the muscles.

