### Sample size

As no clinical trial has evaluated the efficacy of JGT on DOMS, a sample size calculation was impossible. A study estimating the sample size for a pilot study proposed 15 subjects per treatment arm as an optimal sample size for the standardized effect size with 90% power and two-sided 5% significance [8].

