### Statistical analysis

The statistical analysis will be conducted by an independent statistician using SAS version 9.4 (SAS Institute). The significance level will be set at 0.05 in a two-tailed test. All continuous data will be presented as means and 95% confidence intervals (CIs). Categorical data will be reported as frequencies and percentages. The intention-to-treat (ITT) principle will be applied for the primary analysis. The ITT population will include subjects who meet the full analysis set (FAS) criteria, including subjects who had the primary outcomes assessed once or more except for the baseline measures and who took the test drug at least once. Subjects who do not meet the eligibility criteria, those who did not take the test drug throughout the study, and those who have never been evaluated after the screening visit will be excluded from the FAS dataset. The per-protocol set will also be analyzed, which will only include subjects who have completed the study as a supplementary analysis.

The baseline characteristics of the study subjects will be presented using a descriptive analysis for each group. The primary outcome will be the differences between the VAS score with motion measured at various intervals from 0 to 72 h after exercise. A mixed-effect model for repeated measures (MMRM) will be used to assess differences along with the time effect. The dependent variable will be the change in the VAS score (pain with motion) measured from 0 to 72 h after exercise. The model will include treatment and protocol-specified visits as fixed effects, and subjects as a random factor. Dunnett’s test will be used for multiple comparisons. The results of the secondary effective analysis will be analyzed using the same method as for the primary outcome, in the case of continuous variables with time variation. Additionally, Student’s *t* test or Wilcoxon’s signed-rank test will be used to compare results before and after the treatment within each group. Categorical data will be analyzed using the chi-squared test or Fisher’s exact test. Missing values by maximum likelihood will be considered when the MMRM is used. The last observation carried forward method will be adopted for missing values for Student’s paired *t* test, the Wilcoxon signed-rank test, or repeated measures analysis of variance.

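### The primary crossover model has no period term although every subject repeats an exercise chosen as unfamiliar; unequal sequences would bias the JGT estimate, and equal ones cost power

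*Protocol article*

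**What the plan says.** The Statistical analysis section names a mixed model for repeated measures and lists its terms: "The model will include treatment and protocol-specified visits as fixed effects, and subjects as a random factor". The outcome is defined as follows: "The dependent variable will be the change in the VAS score (pain with motion) measured from 0 to 72 h after exercise". Secondary continuous outcomes measured over time use the same method. Neither period nor sequence is mentioned as a model term anywhere in the article, although the Discussion calls the design a 2 × 2 crossover.

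Under Study design, after more than a week, "the subjects will repeat the same process with the other drug". The wash-out is derived from the longest component half-life alone. The exercise section explains that the treadmill task stresses the calf muscles "as it is an unfamiliar eccentric exercise", and the inclusion criteria select men who have not been exercising regularly.

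On allocation: "Subjects will be randomly allocated to either the JGT or the placebo group with equal probability". The list covers 30 subjects in groups A (JGT first) and B (placebo first); an exact 15:15 split is not stated.

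**The concern.** In a two-period crossover, each subject's JGT–placebo difference contains the treatment effect plus or minus the period difference, with the sign set by the sequence. A period term removes the period difference. Without one, it either leaks into the treatment estimate or stays in the error.

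Here the protocol itself supplies a reason to expect a period effect. Soreness is induced by a task chosen for its unfamiliarity, and by the second hospitalization the task is no longer unfamiliar. The wash-out deals with residual drug and not with adaptation to the exercise. Taking the change from the pre-exercise value does not help either, because that baseline precedes the soreness that would differ between periods.

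At stake are the primary estimate and every secondary outcome analysed in the same way, in a trial of only 30 subjects.

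**Working it through.** **Plan's own figures.** The wash-out reproduces: 10 × 14.9 h / 24 = 6.21 days. The sample size cannot be reproduced. The Sample size section states that "a sample size calculation was impossible" and borrows "15 subjects per treatment arm as an optimal sample size for the standardized effect size with 90% power and two-sided 5% significance" without giving an effect size or SD. The size of the period effect and the SD below are therefore assumptions.

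**Inputs.** From the documents: n = 30, sequences A and B, and "The significance level will be set at 0.05 in a two-tailed test". Assumed: SD of the within-subject JGT–placebo difference, sd = 20 mm; period effect π (period 2 minus period 1) of −5, −15 or −20 mm; true effect 0.613 × 20 = 12.3 mm, the value that gives 90% power at n = 30 with a period term.

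**Expected difference by sequence.** Sequence A: τ − π. Sequence B: τ + π. Averaged without a period term:

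E(estimate) = τ − π(nA − nB)/n

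**Unequal sequences, π = −20 mm.**
- 18:12: bias = 20 × 6/30 = +4.0 mm, so JGT looks worse. At 12:18 it is −4.0 mm, in favour of JGT.
- 20:10: bias = 20 × 10/30 = +6.7 mm. Simulated type I error is about 17%.
- At 18:12 type I error stays near 5%, because the inflated error estimate offsets the bias, but power to detect a true benefit falls to about 29%.
- With a period term, simulated bias is about 0 and type I error about 5% at each of these splits.

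**Equal sequences, 15:15, complete data.** The ±π terms cancel, so the estimate is unbiased and its true standard error stays at 20/√30 = 3.65 mm. The estimated variance of the differences, however, becomes about sd² + π² × n/(n − 1). The test then needs a mean difference above t × (inflated SE), with t = 2.045 on 29 df. Approximate power is P{Z > (threshold − 12.3)/3.65}.

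| Fall (mm) | Inflated SD (mm) | Estimated SE (mm) | Threshold (mm) | Approx. power | Simulated power | Simulated type I error |
|---|---|---|---|---|---|---|
| 0 | 20.0 | 3.65 | 7.5 | 90% | 90% | 5.0% |
| 5 | 20.6 | 3.77 | 7.7 | 89% | 89% | 4.4% |
| 15 | 25.2 | 4.59 | 9.4 | 78% | 78% | 1.5% |
| 20 | 28.5 | 5.21 | 10.7 | 67% | 67% | 0.6% |

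With a period term, power stays at 90% for every fall in the table.

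**Limit of this check.** It treats the paired difference per subject as the unit. The listed model, read literally, has one random subject effect and takes its error from visit-level residuals. Simulations of that model under assumed SDs (10 to 12 mm subject-by-period, 10 to 12 mm residual) gave null rejection rates of about 38 to 45% even with no period effect. A period term alone did not correct this. On that reading the correlation of visits within a period is a second defect, and the power losses above do not carry over.

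**The case against.** A reader might infer that any fall in soreness at period 2 biases or swamps the JGT effect. The documents do not support that. At 15:15 with complete data there is no bias for any period effect, and a 5 mm fall costs about one point of power.

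Further objections carry weight:
- **Imbalance is not established.** Under unrestricted allocation of 30, exactly 15:15 has probability 14%, and 18:12 or worse 36%. But the article does not say that allocation is unrestricted, and blocking may be described in the full protocol. Even under simple randomization the bias averages zero over possible allocations. What stands is that a realized imbalance biases that trial's estimate. Losses can also create one, since the Intervention section drops subjects who need medication.
- **The inflated variance is not real variance at 15:15.** Converting it into an equivalent loss of subjects, or putting it into a noncentral t calculation, overstates the loss for the middle case (74% instead of 78%).
- **Visit might be numbered across both hospitalizations,** in which case it would absorb period. This is possible, but the outcome definition and Table 1 index assessments by time after exercise. If the other coding is meant, the text must say so.
- **The size of the fall is unknown.** True: the text supports only its plausibility.

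None of this justifies omitting period. Nor is it detail left to an analysis plan, because the article states the list of fixed effects.

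**Conclusion.** The point holds as a defect in the stated model, with conditional consequences. If the sequences are unequal, by allocation or by loss before period 2, a fraction (nA − nB)/n of the period effect passes into the JGT–placebo estimate, in either direction. If they are equal and complete, the estimate is unbiased but the test is conservative, negligibly so for a small fall and materially so once the fall approaches the SD of the paired differences.

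The conclusion that period belongs in the model rests on the design and on the protocol's own account of why the exercise causes soreness. The millimetre and power figures rest on an assumed SD of 20 mm and assumed falls, and are not predictions for the planned mixed model.

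**What to change.** Before unblinding:

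1. Add period and sequence as fixed effects to the primary model and to the secondary outcomes that use the same method. This costs 2 df. Period × visit is optional: with nine post-exercise times it adds 8 df.
2. Add a subject-by-period random effect, or an equivalent covariance for visits within a period, because a random subject intercept alone ignores that correlation.
3. State that visit means time after exercise within a period, and report the estimated period effect with its confidence interval.
4. If wanted, give a period-1-only comparison of JGT with placebo as a sensitivity analysis, labelled as having low power.

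The cost is a few sentences of analysis wording and a few degrees of freedom. No new subjects, visits or data are needed.

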## Methods and design

### Objective

The aim of this study is to assess the therapeutic effect of JGT in the relief of DOMS symptoms. The primary outcome is the difference between the JGT and placebo groups in pain intensity, measured every 12 h from 0 to 72 h after exercise. Our secondary outcomes include the pain threshold in the calf muscles, calf circumference, and serum markers of muscle damage. Furthermore, exercise-induced shifts in serum and urinary metabolites will be analyzed using a metabolomics-based analysis.

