### Outcome measures

#### Pain intensity

The primary outcome will be the visual analog scale (VAS) score to measure pain with motion. To assess the perception of DOMS after the treadmill exercise, four separate baseline pain intensity measures will be recorded: the NRS score, a VAS with motion, a VAS at rest, and a VAS after walking downstairs. Pain intensity will be measured before the exercise, immediately after the exercise, and 1, 6, 12, 24, 36, 48, 60, and 72 h after the exercise.

The VAS is one of the most widely used measures of pain intensity, determined on a 100-mm horizontal line, where 0 indicates “no pain” and 100 indicates “the worst imaginable pain” [32, 33]. Assessors will record the length of the point marked by the subject. For the NRS pain score, the subjects will be asked to report overall pain intensity on a single 11-point numeric scale, with 0 indicating “no pain” and 10 representing “the worst imaginable pain” [33]. Although studies have shown that both the VAS and NRS have similar sensitivity in pain assessments, the VAS is believed to have a higher degree of precision [34, 35]. However, the NRS has the advantage that it can be used effectively across all types of disorders because it is easy and simple. To take advantage of each method, the VAS will be used to evaluate the detailed pain intensity with motion, whereas the NRS will be used to evaluate the overall pain intensity.

To assess time-weighted overall pain intensity, the sum of the pain intensity differences (SPID), which is an outcome measure that summarizes the treatment response over a period of time, will be calculated using the NRS scores that were evaluated before exercise and at 24, 48, and 72 h after exercise [36]. The SPID_72_ value will be obtained according to the following calculation: (1) PID (pain intensity difference) = NRS_t_ – NRS_baseline_; (2) SPID_t_ = ∑PID_t_ * (time in hours elapsed since the previous observation). A higher SPID_72_ value indicates larger differences in pain intensity over the 72 h after exercise.

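### The primary model lists no term for the hospitalisation, so if fitted as listed it tests JGT against placebo with the wrong error term and the 5% test can be liberal

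*Protocol article*

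**What the plan says.** The Statistical analysis section of the protocol article names the model class: "A mixed-effect model for repeated measures (MMRM) will be used to assess differences along with the time effect". It then lists the terms: "The model will include treatment and protocol-specified visits as fixed effects, and subjects as a random factor". The only random term in that list is "subjects as a random factor". The response is also stated: "The dependent variable will be the change in the VAS score (pain with motion) measured from 0 to 72 h after exercise". The test level is fixed: "The significance level will be set at 0.05 in a two-tailed test".

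The number of scores per stay comes from the Pain intensity section: "Pain intensity will be measured before the exercise, immediately after the exercise, and 1, 6, 12, 24, 36, 48, 60, and 72 h". That makes nine post-exercise scores per hospitalisation. The Objective section describes the primary outcome as "measured every 12 h from 0 to 72 h after exercise", which would make seven. The Study design and Discussion sections describe a 2 × 2 crossover with two hospitalisations more than a week apart, one per drug.

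The listed terms include no period effect, no subject-by-period effect and no treatment-by-visit interaction. No covariance structure is named for scores within one hospitalisation.

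**The concern.** Each subject contributes two profiles of up to nine scores, and each profile follows one bout of exercise under one drug. Treatment is applied to the stay, not to the single score, so the JGT-placebo difference is replicated once per subject and not nine times. Its proper error is how much a subject's two stays differ for reasons other than the drug.

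A subject random effect alone gives compound symmetry over all 18 scores: those from one stay are no more alike than those from two stays. In this trial they probably are more alike, for three reasons:

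- The response is a change score. If each stay's own pre-exercise value is the baseline, all nine changes share its measurement error.
- Soreness from one bout rises and resolves over hours to days, so neighbouring scores move together.
- The weight belt may be 5 to 10 kg, and the article does not say that a subject's load is the same in both stays.

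At stake are the p-value and confidence interval of the primary comparison. The article applies the same method to continuous secondary outcomes measured over time.

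**Working it through.** **Inputs from the article.** n = 30 subjects, each in both periods; T = 9 post-exercise scores per stay (or 7); two-sided level 0.05.

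**Assumed inputs.** The article gives no variance or correlation. I take a residual SD σ_E = 12 mm and a subject-by-period SD σ_SP of 0, 3, 5 or 10 mm. The subject SD cancels from the treatment difference.

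**Formulas (balanced data).**

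- True variance of the treatment difference: 2(σ_SP² + σ_E²/T)/n.
- Variance that the listed model reports: 2·MS/(nT), where MS is the pooled residual mean square on 2nT − n − T degrees of freedom. For T = 9 this is 540 − 30 − 9 = 501.
- Expected MS: [(n−1)(Tσ_SP² + σ_E²) + (2n−1)(T−1)σ_E²]/(2nT − n − T).
- Actual type I error: about 2[1 − Φ(1.96 × reported SE/true SE)].

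**Reproducing the stated 5%.** With σ_SP = 0, E(MS) = 144 and both SEs are √(2 × 144/270) = 1.03 mm. The ratio is 1.00 and the type I error 5.0%. The nominal level holds when the model's own assumption holds.

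**Worked case, σ_SP = 5, T = 9.** E(MS) = [29 × (225 + 144) + 59 × 8 × 144]/501 = (10,701 + 67,968)/501 = 157.0. Reported SE = √(2 × 157.0/270) = 1.08. True SE = √(2 × (25 + 16)/30) = 1.65. Ratio 0.65, so type I error = 2[1 − Φ(1.28)] = 20%.

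| σ_SP (mm) | Reported SE | True SE | Type I error, T = 9: formula | Simulated (20,000 null trials) | T = 7: formula |
|---|---|---|---|---|---|
| 0 | 1.03 | 1.03 | 5.0% | 5.2% | 5.0% |
| 3 | 1.05 | 1.29 | 11.1% | 11.6% | 9.7% |
| 5 | 1.08 | 1.65 | 20.1% | 20.3% | 16.9% |
| 10 | 1.21 | 2.78 | 39.6% | 40.3% | 34.4% |

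The SEs in the table are for T = 9. The SD of 5 mm corresponds to 25/(25 + 144) = 15% of within-subject variance being common to a stay. A share of only 5% already gives a type I error of about 10% with T = 9.

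**Other forms of within-stay correlation (T = 9, simulated, all values assumed).**

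- AR(1) between consecutive scores, no subject-by-period term: about 14 to 15%, 24% and 38% at 0.3, 0.5 and 0.7.
- Correlation decaying with actual hours as exp(−gap/τ): 14%, 24%, 37% and 47% at τ = 6, 12, 24 and 48 h.
- Shared baseline error with SD 0.25, 0.5 or 1 times the residual SD: 11%, 25% and 44%.

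**Single-visit contrast.** If JGT and placebo are compared at one visit with the same pooled residual, the type I error across these settings is only about 5 to 9%.

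**Proper error term.** A paired analysis of each subject's two stay means (29 df), or the same with a period adjustment (28 df), stayed at about 5% in every setting simulated. In balanced data the paired analysis is equivalent to adding a random subject-by-period effect. A fitted within-stay residual covariance was not simulated.

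**The case against.** The strongest defence is that the article names an MMRM. Such a model normally carries a residual covariance for the repeated visits, and an article commonly leaves its structure to the full protocol or SAP. The text does not say that the subject effect is the whole covariance model. If the residual covariance is blocked by subject and hospitalisation, the problem disappears. This stands as a limit on the claim: a reader might infer that the plan commits to a subject effect and nothing else, and the article does not say so.

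It does not dispose of the point. Each visit time occurs twice per subject, once in each stay. A visit covariance blocked on subject alone, as in a parallel-group MMRM, cannot separate the stays without a hospitalisation identifier, and the listed terms supply none. Numbering the visits through both stays would separate them, but an unstructured matrix would then have 18 × 19/2 = 171 parameters from 30 subjects.

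Two other stronger readings also fail. One is that the model treats repeated scores as independent: they are independent only given the subject. The other is that the standard error is certainly far too small. That depends on variances the article does not give, and the loss is nil if there is no excess correlation within a stay. Pre-exercise scores in healthy men may vary little, so the shared-baseline part could be small.

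Finally, the mention of differences at various intervals and of Dunnett's test could mean visit-wise contrasts, where the inflation is slight. The listed terms contain no treatment-by-visit interaction, however, so what they estimate is the treatment main effect.

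**Conclusion.** The point holds in conditional form. The primary model as listed does not fit the crossover, because nothing in it marks the level at which treatment varies. If it is fitted with those terms, the treatment main effect is tested on about 500 degrees of freedom instead of 28 or 29. The test is then liberal whenever scores within a stay are more alike than scores across stays.

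The direction follows from the design; the size does not. For nine scores and an assumed residual SD of 12 mm, the type I error runs from 5% (no excess correlation) through about 12% and 20% to 39 to 40% at subject-by-period SDs of 3, 5 and 10 mm. With seven scores it is somewhat lower. The documents do not establish that the sponsor's final analysis will have this fault, since a covariance blocked by hospitalisation may be specified elsewhere.

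**What to change.** State the hospitalisation in the primary model:

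- Add a fixed period effect.
- Keep the subject random effect and add a random subject-by-period effect; or block the residual covariance by subject and hospitalisation, again keeping the subject effect. Without the subject effect, between-subject variance enters the treatment error and the gain from the crossover is lost.
- If the residual covariance is unstructured, it has 9 × 10/2 = 45 parameters from 60 profiles. Name a simpler fallback in advance, for example AR(1) plus random subject-by-period, in case it does not converge.
- Use Kenward-Roger degrees of freedom.
- Confirm with the paired crossover analysis of each subject's period-mean change in VAS.
- Say whether the primary contrast is the treatment effect averaged over visits or a contrast at named visits, and apply the same structure to the continuous secondary outcomes.

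The cost is a change of analysis wording and wider confidence intervals. No extra data are needed.

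### The primary analysis names no deciding contrast, its model cannot give time-specific treatment differences, and Dunnett's test does not protect JGT-versus-placebo comparisons across visits

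*Protocol article*

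**What the plan says.** All references are to the protocol article.

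- **Endpoint (Statistical analysis):** "The primary outcome will be the differences between the VAS score with motion measured at various intervals from 0 to 72 h after exercise".
- **Endpoint (Objective):** the between-treatment difference in "pain intensity, measured every 12 h from 0 to 72 h after exercise", which is seven times.
- **Measurement times (Pain intensity):** before exercise, then "immediately after the exercise, and 1, 6, 12, 24, 36, 48, 60, and 72 h after the exercise". That is nine times from 0 to 72 h, and Table 1 shows the same nine.
- **Model (Statistical analysis):** "A mixed-effect model for repeated measures (MMRM) will be used to assess differences along with the time effect". Its terms are given as: "The model will include treatment and protocol-specified visits as fixed effects, and subjects as a random factor". No treatment-by-visit term is listed.
- **Multiplicity (Statistical analysis):** "Dunnett’s test will be used for multiple comparisons". The family of comparisons is not stated.
- **Level (Statistical analysis):** "The significance level will be set at 0.05 in a two-tailed test".
- **Treatments (Randomization and allocation concealment):** two only, since "both groups will take JGT and the placebo drug".
- **Timing of the first dose (Table 1):** the first medication mark is in the 19:00 column, 1 h after exercise.

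**The concern.** Three statements in one section do not fit together. The endpoint is worded as several differences at several times. The model allows only one treatment difference, the same at every time. The multiplicity method is built for several treatments against a common control, and this trial has one active treatment.

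At stake is what counts as success. A reader cannot tell whether the claim rests on one overall treatment effect or on a difference at any of several times. The plural endpoint and the stated need for multiple comparisons both suggest a visit-by-visit reading, and under that reading the named procedure gives no protection. The Background says that effectiveness will be demonstrated, so the error rate of the primary claim matters. The same section carries the method over to continuous secondary outcomes measured over time, so the fault is repeated there.

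**Working it through.** **Inputs.** Two-sided level 0.05, two treatments and 30 subjects in a crossover (30 within-subject differences) come from the article. So do the times 0, 1, 6, 12, 24, 36, 48, 60 and 72 h. The correlation of treatment differences between visits is not given; it is assumed exchangeable, with values from 0 to 0.9. The 0.05 is a nominal level, so there is no derived figure to reproduce. The question is which tests it applies to.

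**1. What Dunnett's test does here.** With k active treatments and one control, it adjusts k comparisons. Here k = 1, so its critical value is that of the t test (2.045 on 29 df). In a simulated two-group dataset with 30 values per group, Dunnett's test and the t test both gave p = 0.0218. If the family is instead each visit against baseline, the test does adjust across visits, but the hypotheses concern change in soreness over time. Neither use adjusts JGT-versus-placebo comparisons across visits.

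**2. What the model gives.** With treatment and visit as main effects only, there is one treatment contrast (1 df). It cannot vary by time, so it cannot answer an endpoint worded as differences at various times.

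**3. If that one contrast is the primary test.** There is a single test, so the visits add no multiplicity. In 40,000 simulated null trials per setting, one test on each subject's average difference over seven visits rejected in 4.8% to 5.0%.

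The contrast is diluted, however. In Table 1 the 0 h score precedes the first dose, and the 1 h score shares its slot. Assume that all nine times enter with equal weight, the data are complete, and a constant effect δ is present only from 6 h. The estimate is then (7 × δ + 2 × 0)/9 = 0.78 δ.

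**4. If JGT and placebo are compared at each visit at 0.05.** Under independence the family-wise error is 1 − 0.95^m:

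- m = 7 (6 to 72 h, after the first-dose slot): 1 − 0.698 = 30.2%
- m = 6 (the 12-hourly grid without 0 h): 1 − 0.735 = 26.5%
- m = 9 (all times from 0 h): 1 − 0.630 = 37.0%

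With correlated visits (40,000 simulated null trials of 30 paired differences per setting):

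| Assumed correlation | 7 times | 9 times |
|---|---|---|
| 0.3 | 27.5% | 32.9% |
| 0.5 | 23.3% | 27.4% |
| 0.7 | 17.9% | 21.1% |
| 0.9 | 11.7% | 12.6% |

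The seven-time column is the relevant one. The nine-time column counts 0 h and 1 h, where a JGT effect could hardly be claimed.

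**5. With a valid adjustment.** Bonferroni over seven visits uses 0.05/7 = 0.0071 per visit. The simulated family-wise error was 4.7% to 1.9% for correlations of 0 to 0.9. Holm is also valid and rejects at least as often.

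**6. Time grid.** Every 12 h from 0 to 72 h gives 0, 12, 24, 36, 48, 60 and 72 h. The Pain intensity section and Table 1 add 1 h and 6 h. The article does not say which set enters the primary analysis.

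**The case against.** The strongest reply is that the listed model has exactly one JGT-placebo contrast. A model that cannot produce per-visit treatment tests cannot inflate the error through them. This stands. A reader might infer from the plural endpoint that no single test exists and that the 5% level is broken. The article does not support that: tested once, the treatment effect of the listed model carries no multiplicity over visits. The inflation is conditional on visit-by-visit testing, which the wording suggests but does not fix.

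A second reply is that the article condenses a fuller protocol, and that the deciding contrast, the interaction term and the comparison family may be set out there or in an SAP. This stands for omissions as such. It does not excuse what is positively stated: a named procedure that does nothing for a two-treatment comparison, an endpoint that does not match its model, and two different time grids.

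Third, the correlations are assumptions, and Dunnett's test for visits against baseline is a coherent use. Both are true. But every correlation in the range gives an error well above 5%, and the baseline use does not bear on JGT.

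Finally, treatment-by-visit is not needed to test an average over all visits entered, because with complete data the additive model already estimates that average. This also stands. The term is needed for per-visit differences and for an average over a chosen subset of visits.

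**Conclusion.** Wrong as written and worth correcting, but not of the highest severity, because one natural reading of the model leaves a single test. The primary contrast is not fixed, the endpoint and the model do not match, and Dunnett's test gives no protection to JGT-versus-placebo comparisons across visits.

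The size depends on the reading:

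- **Single treatment effect:** no inflation from the visits, but an estimate of about 78% of a constant post-dose effect if 0 h and 1 h are included on equal terms. The 5% level also presumes a covariance structure that fits the repeated measures, which is a separate matter and is not judged here.
- **Visit-by-visit comparison:** family-wise error of about 28% to 12% over the seven times from 6 to 72 h for assumed exchangeable correlations of 0.3 to 0.9, and 30% if independent.

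The article therefore does not assure the 5% level. It does not show that the level is breached.

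**What to change.** 1. Name one primary contrast. An example is the JGT minus placebo least-squares mean difference in VAS with motion, averaged over a stated set of post-dose visits and tested once at two-sided 0.05. State whether the 6 h visit belongs to the set.
2. Add treatment-by-visit to the model so that per-visit differences can be estimated.
3. Report the per-visit differences as secondary, with Holm or Hochberg adjustment.
4. Replace Dunnett's test for the treatment comparisons. If it is kept for visits against baseline, say so and label it as describing the time course.
5. Reconcile the 12-hourly grid in the Objective with the nine times in the Pain intensity section and Table 1.
6. Apply the same wording to continuous secondary outcomes measured over time.

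The cost is wording only, with no change to sample size or visits. The downside is that a result at a single time loses primary status, and an average may understate an effect confined to a few hours. The contrast must be fixed before unblinding. If the full protocol or an SAP already fixed it, the article should state that choice.
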